### Study objectives

The primary objectives are: 1) to qualitatively explore the impact of *Fit for Dialysis* on the knowledge/attitudes of patients, family caregivers, and health care practitioners regarding the importance of exercise-based principles of wellness, and in what ways this is effective in educating, motivating, or sustaining patient exercise during dialysis, at home, and in the community; 2) to quantitatively examine levels of adherence to exercise prescription, and qualitatively explore the factors influencing adherence (e.g. *Fit for Dialysis*, experience of adverse events); and 3) to quantitatively explore the impact of *Fit for Dialysis* on patient physical fitness and activity outcomes.

The secondary objectives are: 1) to qualitatively explore factors related to family caregivers that may impact the successful uptake of the key messages of *Fit for Dialysis*; 2) to qualitatively explore the factors related to nephrologists, nurses, and hospital administrators that may impact the successful uptake of the key messages of *Fit for Dialysis*; and 3) to qualitatively explore factors related to patients’ home and community environments that may impact the successful uptake of the key messages of *Fit for Dialysis*.

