*Exercise Logs*: During the 16-week intervention, an intradialytic exercise log will be kept by the PTAs documenting exercises performed by the patients, as well as perceived exertion and heart rate. Patients will also be asked to keep a log of the exercises performed at home and in the community. The PTAs will review the exercise logs with the patients prior to each intradialytic exercise session to discuss any concerns.
*Adherence*: Adherence is important to assess as it is a necessary step to achieve gains in physical fitness (which would, in turn, lead to broader health benefits). However, there is no gold standard for assessing adherence to exercise, particularly in an elderly dialysis population. We have based our exercise prescription and definition of adherence on clinical judgement and prior experience providing exercise to frail older HD patients [19]. Adherence is thus defined as meeting at least 70% of the exercise prescription (recognizing that the number of minutes of prescribed exercise per week may change during the protocol as patients improve their fitness level with exercise), on average, over the 16-week intervention [67]. Given the separate components of exercise (intradialytic and home/community-based) that are being targeted by our intervention, we will include both a global adherence measure and separate adherence measures for the two exercise components (intradialytic and home/community). This same definition of adherence will be used for the intradialytic exercise and home/community exercise components. In addition, a global dichotomous measure of adherence will be used to facilitate inclusion in a multivariable model in which patients will be considered adherent overall if they are adherent (at least 70% of the exercise prescription) to both intradialytic and home/community exercise components, and non-adherent otherwise.

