### Sample size

Sixty patients (30 in the film + exercise hospital, 30 in the exercise-only hospital) will be recruited. Thirty patients per study site is the minimum recommended for early phase studies to provide reasonable estimates of efficacy on outcomes (estimating means and variances) [68–70]. A total sample size of 60 will facilitate building a multivariable model with up to 3 covariates plus 3 main factors (hospital, time, and hospital X time). Moreover, with alpha = 0.05 and power of 80%, we would need about 30 patients per arm to detect a 0.65 SD difference between hospitals in the 2MWT, our primary quantitative outcome. A 0.65 SD difference represents a moderate effect size and is equivalent to about 22 m, which is larger than the minimum clinically important difference for the 2MWT [71]. Based on the pilot study with older HD patients [19] conducted by several co-investigators, there was 0 attrition over the duration of the exercise program. Although we recognize that the observed attrition rate may be higher than this in the present study, estimating attrition is a specific aspect of feasibility that we will be evaluating in this phase of the research. Sample size calculations for early phase studies commonly do not include adjustments for attrition [68–70].

Patients (*n* = 20; 10 per site), family caregivers (*n* = 20; 10 per site), nephrologists (*n* = 10; 5 at each site) and nurses (*n* = 20; 10 at each site) will be selected to participate in qualitative semi-structured interviews (Section 4.5.1). Sample sizes are consistent with what is deemed sufficient for qualitative sampling in a homogeneous group within a single setting, and provides a sufficient number of participants to facilitate saturation [72].

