Quantitative analysis of exercise prescription adherence (intradialytic and home/community exercise components) will be examined. To determine if patients are adherent to the intradialytic component, PTA-recorded minutes of intradialytic exercise performed each week will be compared to the prescription for that week (e.g. 50 min in week 3 were done, 60 min were prescribed, which is 83% adherent). Similarly, for the home/community component, adherence will be based on weekly number of minutes of exercise performed based on the GLTEQ results compared to the weekly exercise prescription. Multivariable logistic regression for each adherence variable will be performed at 8 weeks (mid-intervention), 16 weeks (end of intervention), and 12 weeks post-intervention including hospital as the main predictor. Covariates including age and sex will be included in the model based on clinical judgment guided by our prior work [19] and the literature.

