To explore the impact of *Fit for Dialysis* on patient fitness and activity outcomes, while keeping in mind the phase of research, our focus is to estimate change in each of the 6 measures using a hospital X time linear repeated measures model for each outcome. The 2MWT is our primary outcome. Examining hospital-level effects will allow us to determine if the two hospitals were similar at baseline. Examining time effects within each hospital will provide information on the effects of the intervention in that hospital (film + exercise or exercise-only). Additionally, examining the hospital X time interaction will allow us to determine the additional effect of the film in addition to the exercise intervention. Since this is an early-phase intervention trial and it is unclear which of our quantitative outcomes will be most responsive in this population, we will also examine the responsiveness of each of the 6 outcome measures using standardized response mean to gauge whether the film + exercise is associated with a small, moderate, or large effect size [78] for each outcome. Covariates will be similar to Primary Objective 2. To examine the impact of adherence on the 2MWT, we will include a dichotomous variable reflecting global (intradialytic and home/community-based exercise considered together) adherence (yes/no). We will also explore including the two separate adherence components (intradialytic and home/community) in the repeated measures model, recognizing the risks of collinearity and model over-fitting (with 8 variables and 60 patients, including an interaction term between the two adherence variables).

As an exploratory analysis to get an initial sense of the temporal effects of both the film and the exercise program, we will calculate change scores for each of the 6 measures from baseline to 8 weeks, from 8 to 16 weeks, and from 16 weeks to 12 weeks after the end of the intervention (i.e. 28 weeks after baseline). An additional exploratory analysis will examine the six outcome measures (DASI, GLTEQ, TUG, 2MWT, Grip Strength, and pedometer) at 12 weeks after the end of the intervention. This analysis will consist of a linear repeated measures model similar to above, with two time points (8 and 16 weeks) and 12 weeks follow-up, and will examine whether any observed gains during the intervention period persist, continue to improve further, or become attenuated over time in both the film + exercise and exercise-only hospitals.

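### Adherence is computed as a graded percentage of prescribed minutes, but the only stated hospital comparison is a logistic model on a 70% cut, which discards information and usually costs power

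*Protocol article*

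**What the plan says.** All references are to the Protocol article.

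- **Study objectives.** The quantitative part of the second primary objective is "to quantitatively examine levels of adherence to exercise prescription".
- **Analysis.** Minutes performed each week are divided by minutes prescribed. The worked example is 50 of 60 minutes, or 83%. Intradialytic minutes come from the assistants' records and home/community minutes from the GLTEQ.
- **Data collection, Adherence.** A patient is adherent on a component when the 16-week average reaches 70% of prescription. For the overall yes/no variable the patient must pass on both components: "In addition, a global dichotomous measure of adherence will be used to facilitate inclusion in a multivariable model". The section also accepts that "there is no gold standard for assessing adherence to exercise, particularly in an elderly dialysis population" and rests the definition on clinical judgement, prior experience and one cited source.
- **Analysis, adherence.** "Multivariable logistic regression for each adherence variable will be performed at 8 weeks (mid-intervention), 16 weeks (end of intervention", and again at 12 weeks post-intervention. Hospital is the main predictor, and the covariates include age and sex.
- **Analysis, fitness outcomes.** For the 2MWT model, "we will include a dichotomous variable reflecting global (intradialytic and home/community-based exercise considered together) adherence (yes/no". The two component variables may also be explored in that model.

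No between-hospital analysis of the percentage itself is stated.

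**The concern.** The objective asks how much of the prescription patients complete, and the data answer that on a graded scale. The stated analysis asks only whether each patient crosses 70%. In a component-specific logistic model, a patient at 35% counts the same as one at 65%, and one at 75% the same as one at 95%.

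The reason given for the overall dichotomy, ease of entry into a multivariable model, does not require a cut. A percentage enters a linear model directly, as outcome or as covariate.

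Three things are at stake. A real hospital difference in a primary-objective outcome is more likely to be missed with 30 patients per hospital. The estimate passed to the planned Phase III cluster trial is an imprecise odds ratio rather than a mean and SD. And if a supervised programme leaves most patients adherent, the logistic model rests on very few non-adherent patients.

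**Working it through.** **Inputs from the protocol (Sample size).** 30 patients per hospital, alpha 0.05 and 80% power. The target effect is stated as follows: "to detect a 0.65 SD difference between hospitals in the 2MWT, our primary quantitative outcome". Sidedness is not stated.

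**Assumptions, not in the protocol.** The 0.65 SD is borrowed for adherence. The percentage is roughly normal with equal SD in both hospitals. Between 20% and 80% of the exercise-only hospital is adherent.

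**Step 1: the plan's own figure.** n per arm = 2[(z_α + z_β)/d]².
- One-sided 0.05: 2[(1.645 + 0.842)/0.65]² = 29.3, so 30. This reproduces the stated number.
- Two-sided 0.05: 2[(1.960 + 0.842)/0.65]² = 37.2, so 38.

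At 30 per arm, the t-test has 69.7% power two-sided and 80.0% one-sided. The comparison below is two-sided, so its starting point is about 70%.

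**Step 2: the same shift after a cut.** If a proportion p₀ is adherent in the exercise-only hospital, the film hospital has p₁ = Φ(Φ⁻¹(p₀) + 0.65). For p₀ = 0.70, Φ⁻¹ = 0.524, the sum is 1.174, and p₁ = 0.880. Power is the exact sum over Binomial(30, p₀) × Binomial(30, p₁) of outcomes where the likelihood-ratio statistic for hospital exceeds 3.841.

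| p₀ | p₁ | Power, cut at 70% | Loss against 69.7% |
|---|---|---|---|
| 20% | 42.4% | 49.6% | 20.1 points |
| 30% | 55.0% | 51.2% | 18.5 |
| 40% | 65.4% | 51.9% | 17.8 |
| 50% | 74.2% | 50.5% | 19.2 |
| 60% | 81.7% | 49.0% | 20.7 |
| 70% | 88.0% | 44.1% | 25.6 |
| 80% | 93.2% | 36.3% | 33.4 |

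The smallest loss, 17.6 points, is at p₀ near 37%. One-sided, the losses are 17.6 to 32.1 points. By the normal approximation, 80% two-sided power on the cut needs about 60 to 104 per arm over this range, against 38 for the percentage.

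**Step 3: sensitivity to shape (simulated, 30 per arm).**
- Bounded, beta-shaped percentages cut at 0.70: t-test about 69%, cut 37–59%, loss about 10 to 31 points.
- Right-skewed log-normal shapes: losses from about 1 to 20 points, depending on the parameters.
- Bimodal adherence, with the film moving patients from a low to a high group: t-test 60–68%, cut 59–70%. There is essentially no loss, and sometimes a small gain.

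**Step 4: number of non-adherent patients.** Expected count = 30(1 − p₀) + 30(1 − p₁).
- p₀ = 0.70: 30 × 0.30 + 30 × 0.120 = 12.6, or 12.6/3 = 4.2 per term for hospital, age and sex.
- p₀ = 0.80: 30 × 0.20 + 30 × 0.068 = 8.0, or 8.0/3 = 2.7 per term.

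**The case against.** **The effect is borrowed.** A reader might infer that the plan assumes 0.65 SD for adherence and therefore loses a fixed 18 to 33 points. The documents do not support that. The 0.65 SD is stated for the 2MWT alone, and no effect, SD or expected rate is given for adherence. This objection stands, and the figures are an illustration.

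**The shape matters.** The film is meant to motivate uptake, so a split into patients who exercise and patients who do not is plausible, and then the cut loses nothing. This also stands.

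**The percentage has its own problems.** The GLTEQ counts bouts of 15 minutes or more and takes in housework and recreation. Minutes must be derived from it, home activity can exceed the prescription, and no cap is stated. A threshold is robust to this and an uncapped mean is not. That shapes the fix. It does not rescue the cut as the sole analysis, because the cut is made on the same derived number.

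**The two-component rule is deliberate.** A reader might infer that a patient with 100% intradialytic and 69% home exercise is treated everywhere like one with 0% on both. That is true only of the overall variable; the intradialytic variable separates them. For the same reason, pooling total minutes would change the question, because surplus home activity could offset missed intradialytic exercise.

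**Other analyses help.** GLTEQ scores and pedometer steps are modelled without a cut, so changes in activity on one side of 70% are not wholly invisible. Those measures are not relative to the prescription, though. The Adherence text also mentions an overall measure before adding the dichotomous one, which may hint at a graded form, but no analysis of it is stated.

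**Early phase, one hospital per arm.** Greater precision cannot separate the film from the site, and no stated decision hangs on this p-value. That limits the consequence. An estimation study still gains from a mean and SD.

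**Conclusion.** The point holds as a mismatch between objective and analysis. A graded percentage is available, levels of adherence are the objective, and the only stated hospital comparison uses a yes/no cut, as does the main adherence term in the 2MWT model.

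Under a roughly normal percentage, a borrowed 0.65 SD difference and 20–80% adherence in the exercise-only hospital, two-sided power at 30 per hospital falls from about 70% to 36–52%. The loss is smaller for some skewed shapes and about nil for a bimodal one. The likely sparsity does not depend on the test chosen: with 70–80% adherent in the exercise-only hospital, about 8–13 of 60 patients would be non-adherent, which is few for a model with hospital, age and sex.

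A reader might also infer that the 70% threshold is unsupported. The protocol does cite a source for it, not available here, and a prespecified threshold is legitimate as a summary. The weakness is its use as the sole analysed form.

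**What to change.** - Make the mean percentage of prescribed minutes completed the main adherence outcome, separately for the intradialytic and home/community components.
- Compare hospitals by linear regression with the same covariates and robust or bootstrap standard errors. Report the mean difference with its 95% CI.
- Cap the weekly percentage at 100%, or report a capped sensitivity analysis, and state how minutes are derived from the GLTEQ.
- Keep the 70% classification, including the both-components rule, as a supportive proportion with its CI.
- In the 2MWT model, replace the yes/no variable with the two component percentages or their capped average. Do not pool total minutes across components.

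**Cost.** The analysis wording changes and the GLTEQ derivation and cap need a sentence; no new data are collected. A mean difference is slightly harder to present than a proportion adherent, and a bounded or skewed percentage needs the robust errors. If adherence proves bimodal, the change gains little power, and the supportive proportion will show the split.

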**Methods/Design:**

This 2-site parallel intervention trial will recruit 60 older hemodialysis patients from two urban hospitals. The trial will compare the film + a 16-week exercise program in one hospital, with a 16-week exercise-only program in another hospital. Physical fitness and activity measures will be performed at baseline, 8 and 16 weeks, and 12 weeks after the end of the program. These include the 2-min Walk Test, Grip Strength, Duke Activity Status Index, and the Timed Up-and-Go Test, as well as wearing a pedometer for one week. Throughout the 16-week exercise program, and at 12 weeks after, we will record patients’ exercise using the Godin Leisure-time Exercise Questionnaire. Patients will also keep a diary of the exercise that they do at home on non-dialysis days. Qualitative interviews, conducted at baseline, 8, and 16 weeks, will explore the impact of *Fit for Dialysis* on the knowledge/attitudes of patients, family caregivers, and nephrology staff regarding exercise for wellness, and in what ways the film is effective in educating, motivating, or sustaining patient exercise during dialysis, at home, and in the community.

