**Discussion:**

This research will determine for whom *Fit for Dialysis* is effective, why, and under what conditions. If *Fit for Dialysis* is proven beneficial to patients, nephrology staff and family caregivers, research-based film as a model to support exercise promotion and adherence could be used to support the National Kidney Foundation’s guideline recommendation (NKF-KDOQI) that exercise be incorporated into the care and treatment of dialysis patients.

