Our study of *Fit for Dialysis* will generate a rich data set for understanding the nature and extent of the impact of the film, for whom it is effective (patients, family caregivers, health care practitioners) and why, and under what conditions. Our study will further facilitate understanding of the actual degree of adoption of exercise, the extent to which and the reasons why the adoption occurred as intended, and the factors important for replication [35]. Further, by using a two-site design, we will generate data that will inform the design of a Phase III, cluster-randomized controlled trial of this intervention.

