### Study setting

Hospital A is a dialysis unit serving 318 patients in an acute care hospital in urban central Canada. Hospital B is a dialysis unit serving 210 patients in an acute care hospital in urban central Canada. The two study settings have similar populations of patients and nurse staffing mix. Neither has an existing exercise program as part of their renal program. Both hospitals are fully supportive of this proposal. Both hospitals will receive the exercise program, and an independent researcher will select which of the two sites will receive *Fit for Dialysis* using the following random allocation rule: roll a single 6-sided die and allocate the active intervention site to Hospital A if the number on top of the die is even or to Hospital B if the number is odd [43].

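### With one hospital per arm, the hospital-by-time interaction estimates a difference in change between two hospitals and cannot be read as the effect of the film

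*Protocol article*

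**What the plan says.** The Abstract (Methods/Design) sets out the comparison: "The trial will compare the film + a 16-week exercise program in one hospital, with a 16-week exercise-only program in another hospital". Under Study setting, which site receives the film is settled by one throw: "roll a single 6-sided die and allocate the active intervention site to Hospital A if the number on top of the die is even", and to Hospital B otherwise. Patients are not randomized.

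The model described under Sample size and Analysis contains hospital, time and their interaction, plus up to three covariates. It has no film term distinct from hospital. The Analysis section interprets the interaction as follows: "examining the hospital X time interaction will allow us to determine the additional effect of the film in addition to the exercise intervention". The 2MWT is the primary quantitative outcome, and the same model is used for all six fitness and activity measures. The adherence logistic regressions also use hospital as the main predictor.

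The Sample size section says that "with alpha = 0.05 and power of 80%, we would need about 30 patients per arm to detect a 0.65 SD difference between hospitals".

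The section on the individualized exercise program assigns one physiotherapy assistant (PTA) to each hospital. That person supervises intradialytic exercise and also collects the fitness and activity outcomes. The article nowhere says that the film effect is confounded with site.

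**The concern.** The die roll makes the choice of site fair, but it provides no replication. Every patient who sees the film is at one hospital and every patient who does not is at the other. A difference in change between the groups is therefore the film effect plus whatever else made the two hospitals diverge over the 16 weeks and the follow-up, and the data cannot divide the two.

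If the sentence stands, a significant interaction for the 2MWT could be reported as the film working when two hospitals without a film could have produced it. A null result is equally ambiguous, because opposite site drift could mask a real effect. The interval and p-value from a patient-level model would also look more precise about the film than the design allows.

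**Working it through.** **Inputs from the article.** One hospital per arm (Abstract, The intervention). Allocation by hospital (Study setting). 30 patients per hospital, alpha 0.05, power 80%, 0.65 SD, equated to about 22 m (Sample size). Model terms hospital, time and hospital by time (Sample size, Analysis).

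**Assumed input.** The ICC of change, ρ, meaning the share of the variance of patients' change that lies between hospitals. The article gives no value, so 0.01, 0.02 and 0.05 are used as a range.

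**1. The plan's own figure.** For two independent groups, n per arm = 2 × ((z_α + z_β)/0.65)².
- One-sided 5%: 2 × ((1.645 + 0.842)/0.65)² = 29.3, so 30. This reproduces the stated figure.
- Two-sided 5%: 2 × ((1.960 + 0.842)/0.65)² = 37.2, so 38.

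Sidedness is not stated and is a separate matter. What matters here is that the 30 comes from a formula for independent patients with no hospital-level variance.

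**2. Degrees of freedom.** Between-hospital df = hospitals − arms = 2 − 2 = 0. Recruiting more patients at the two sites does not change this.

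**3. What the interaction does and does not remove.** The hospital main effect absorbs a stable difference in level. The interaction still contains anything that makes change differ by site: how each PTA supervises or measures, unit practice, local events, case mix that affects response, and differential attrition. Under the section on the film, the PTA at the film hospital watches it after baseline data collection. Follow-up measurements in that arm alone are therefore taken by someone who has since seen the film. Age and sex as covariates cannot adjust for hospital-level factors.

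**4. Size of the understatement if the result is read as a film effect.** Consider one change contrast with total variance 1 and m = 30 per hospital.
- True variance of the difference: 2 × (ρ + (1 − ρ)/m).
- Variance the patient-level model reports: 2 × (1 − ρ)/m, because the residual contains only within-hospital variation.
- Ratio of standard errors: √[(1 + (m − 1)ρ)/(1 − ρ)] = √[(1 + 29ρ)/(1 − ρ)].
- Actual rejection rate of a nominal 5% two-sided test: 2 × P(t₅₈ > 2.002/ratio).

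| Assumed ρ | (1 + 29ρ)/(1 − ρ) | SE ratio | Rejection rate with no film effect |
|---|---|---|---|
| 0.01 | 1.29/0.99 = 1.303 | 1.14 | 8.5% |
| 0.02 | 1.58/0.98 = 1.612 | 1.27 | 12.0% |
| 0.05 | 2.45/0.95 = 2.579 | 1.61 | 21.8% |

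**5. The same in metres.** The SD implied under Sample size is 22/0.65 = 33.8 m. If that SD applied to change, which the article does not say, the SD of a pure hospital difference, √(2ρ) × 33.8, would be 4.8, 6.8 and 10.7 m, against the 22 m target.

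**The case against.** The strongest defence is that this is a declared early-phase study. The paragraph on fitness outcomes speaks of exploring and estimating, asks the reader to bear the phase in mind, and sets no decision rule for the interaction. The power sentence refers to a difference between hospitals, not to the film. Several features limit site differences: one blinded physiotherapist prescribes at both hospitals, the PTAs belong to neither, neither unit has an existing exercise program, and interviews compare barriers between hospitals. Staff encouragement prompted by the film is also part of its effect, not a confounder.

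All of this is fair. It makes the design acceptable for estimation and feasibility and reduces the likely size of site drift. It does not remove the aliasing, and it does not support a sentence claiming to determine what the film adds.

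A reader might also infer four stronger points that the article does not support:

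- **That the error rates and intervals are wrong outright.** They are not wrong for the difference in change between these two hospitals. They mislead only when read as a film effect, and by an amount that depends on an assumed ICC.
- **That the baseline comparison is a failed remedy for confounding.** The article says "Examining hospital-level effects will allow us to determine if the two hospitals were similar at baseline", but does not offer this as a repair, and stable level differences are absorbed by the hospital term in any case.
- **That the trial promises an ICC for Phase III.** It says "by using a two-site design, we will generate data that will inform the design of a Phase III, cluster-randomized controlled trial", and no passage names an ICC among the things it will supply.
- **That the article announces proof of benefit.** The phrase "is proven beneficial to patients, nephrology staff and family caregivers" (Abstract, Discussion) follows an 'if' and is not an analysis rule.

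**Conclusion.** The point holds as a matter of interpretation. Film and hospital are completely aliased, there are 0 df for between-hospital variance, and the Analysis section attributes to the film a contrast that can only describe two hospitals. This follows from the design and needs no assumed figure.

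The size of the false precision is conditional. With 30 per hospital and an assumed ICC of change of 0.01 to 0.05, the standard error is understated by a factor of 1.14 to 1.61, and a nominal 5% two-sided test rejects 8.5% to 21.8% of the time when the film does nothing. These figures treat the two hospitals as draws from a wider population and use a single change contrast in place of the full repeated measures model. At an ICC of zero there is no inflation, but this trial cannot show that the ICC is zero.

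**What to change.** 1. In Analysis, replace the claim about the interaction with: *estimate the difference in change between the two hospitals, which cannot be separated from other site differences*.
2. Report that difference as an estimate with a confidence interval, state that the interval excludes between-hospital variance, and attach no p-value to a film effect.
3. In Sample size, state that the power applies only to a difference between these two hospitals.
4. Apply the same caveat to the adherence regressions that use hospital as the main predictor.
5. Add a sensitivity table multiplying the standard error by √[(1 + 29 × ICC)/(1 − ICC)] for assumed ICCs from 0.01 to 0.05. If the numbers analysed differ from 30 per hospital, change the multiplier to match.

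The cost is some rewording and one small table. Recruitment, conduct and data collection are unchanged. The downside is a weaker claim about the film.
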